**Figure 1 figure1:**
[figure not shown]
Good School Toolkit programmatic theory of change.

The Good School Toolkit is one of the few school interventions with a demonstrated impact of reducing school violence in a resource-constrained setting, including teacher-to-student violence [25]. The Good Schools Study included a cluster randomized controlled trial [26,27], qualitative study [28], process evaluation [29], and economic evaluation [30]. During the trial, conducted in Luwero district in Uganda from 2012-2014, the toolkit was delivered to 21 intervention schools that were compared with 21 wait-list control schools. The trial found that the toolkit reduced the relative risk of past-week teacher-to-student physical violence by 42% [27]. Secondary trial analysis found that the toolkit reduced teacher-to-student past-week physical, emotional, or sexual violence (adjusted odds ratio [OR] 0.41, 95% CI 0.26-0.64) and any student-to-student past-week physical, emotional, and sexual violence (adjusted OR 0.70, 95% CI 0.51-0.96) [31,32]. Subsequently (from 2015), the toolkit was delivered to 19 of the wait-list control schools. While the intervention remained the same (see Table 1), during later delivery the intervention was implemented by *resource persons*, trained and supported by Raising Voices, rather than the Raising Voices program team.

**Table 1 table1:** The Good School Toolkit intervention delivered during the trial and later delivery to study schools.

TIDieR [33] guideline	Description of the toolkit
Brief name	Good School Toolkit
Why	The goal of the toolkit was to transform the operational culture at the school level such that violence against children is prevented. The toolkit draws on the Transtheoretical Model [34] and contains behavior change techniques that have been shown to be effective in a variety of fields [35] and have been included in interventions to change teacher behavior in primary schools [36,37] and reduce perpetration of intimate partner violence [38].

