Who provided	Delivery to trial schools: Raising Voices program staff members were trained facilitators and advocates and had received approximately 100 hours of training with individualized coaching support to understand the ideas and content of the toolkit. Later delivery to schools: Raising Voices resource persons were experienced consultants, usually working within the education sector who received at least 20 hours of training and then subsequent individualized coaching support by Raising Voices program staff to understand the ideas and content of the toolkit and how to provide support to school-based protagonists. The key protagonists in each school were 2 teachers who receive 3-day residential workshop based training and ongoing support.
How	During the intervention, Raising Voices staff or resource persons provided direct one-on-one support in the form of in-person visits and telephone calls to staff protagonists, and in-person visits to student protagonists. Staff and student protagonists conducted face-to-face activities with other staff and students in their school, mainly in groups. Children and staff members encouraged others to form, lead, and join groups for various intervention activities.
Where	Activities with students and staff were conducted in schools. Some activities involved creating a better school environment by painting murals on school walls and hanging codes of conduct in visible places; however, the intervention does not require any physical infrastructure.
When and how much	Raising Voices staff made in-person visits to protagonists in each school quarterly and telephoned school staff members approximately monthly, although this varied slightly depending on need. The toolkit itself was designed to be implemented flexibly, and there was no prescribed number of activities or set schedule upon which they should be implemented. However, schools should proceed in sequence and conduct a minimum number of activities, which depends on the stage, prior to progressing to the next stage.

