Tailoring, modifications, fidelity	The toolkit was specifically designed to be flexible and adaptable to individual schools. To ensure more uniformity during the trial, Raising Voices staff visited each school at least once per school term, conducted a 3-day residential workshop with all teacher protagonists, met with protagonists to review progress after 1 to 2 terms of implementation, and held meetings with protagonists so they could learn from each other.

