### Regression Analysis Strategy

All analysis is exploratory and hypotheses generating rather than testing. To explore if the intervention influences later outcomes, we will compare across the trial and no exposure groups (1 vs 2.2) and original study arms (1 vs 2) first including all 42 schools and then repeated, dropping the 2 nonimplementation schools. To further explore differences between levels of exposure, we plan to compare between trial and the later delivery groups (1 vs 2.1) and across secondary exposure groupings (Figure 3). We will account for clustering by including original study primary school as a random effect in mixed-effect regression models [71]. Binary outcomes will be analyzed using mixed-effect logistic regression, with effect size presented as odds ratios. Continuous outcomes will be analyzed using mixed-effects linear regression, with effect size presented as mean difference. All unadjusted and adjusted analyses will include baseline school-level mean of outcomes, where available [72]. Adjusted models will additionally include covariates identified as potential confounders. All measures of effect will be presented with 95% confidence intervals and *P* values. Size and direction of effect will be considered along with *P* values when assessing the strength of associations [70]. Appropriate methods will be used to analyze numeric outcomes that are not normally distributed. For example, bias-corrected 95% confidence intervals will be estimated using nonparametric bootstrapping. The presence of effect modification will be assessed by comparing models fitted with and without an interaction term. Likelihood ratio tests with *P* values<.1, along with the direction and size of effect for each group, will be considered as evidence for or against modification. If there is evidence of modification, then stratum-specific effects will be calculated [73].

For self-reported exposure, propensity score–matching will be used to account for the likelihood that self-reported exposure is confounded by an individual’s propensity to report exposure. We will estimate what factors predict toolkit exposure using regression analysis [29], then calculate predicted probability of exposure and group adolescents with similar propensity scores. The analysis will compare outcomes across these propensity score exposure groups, including the score as a covariate in regression models [72].

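### The trial versus later delivery contrast (1 vs 2.1) is framed as levels of exposure, but it also varies provider, timing and grade mix; match it on grade and describe it as a joint contrast

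*Protocol article*

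**What the plan says.** The protocol article defines its groups under Good School Toolkit Exposure Measures (Primary). Group 1 is all participants from the 21 trial intervention schools. Group 2.1 is participants who were in Primary 5 or 6 at Wave 1 in the 19 wait-list schools that took up the toolkit from 2015. Wave 1 drew on Primary 5 to 7 (Sampling, Intervention Delivery, and Survey Assessments), so group 1 contains all three grades.

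Regression Analysis Strategy introduces the contrast with: "To further explore differences between levels of exposure, we plan to compare between trial and the later delivery groups (1 vs 2.1". The same paragraph calls all analysis exploratory.

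The section on the intervention states that the toolkit itself did not change between phases, but that resource persons took over implementation in the later one. It describes them as "trained and supported by Raising Voices, rather than the Raising Voices program team". In the Who provided row of Table 1, program staff "had received approximately 100 hours of training with individualized coaching support", while resource persons were experienced consultants "who received at least 20 hours of training and then subsequent individualized coaching support by Raising Voices program staff".

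Under Potential Confounders and Effect Modifiers, Wave 1 school grade is among the variables to be used as appropriate for the relationship studied. Provider is not listed.

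**The concern.** Calling two groups levels of exposure suggests that they differ in how much of one thing they received. Here at least four things change together: expected duration, timing, provider and grade mix. If group 1 does better than group 2.1, the cause could be longer exposure, earlier exposure, more highly trained support, or the presence of older Primary 7 pupils in group 1 only. If no difference appears, these could offset each other.

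The Discussion says the analysis will inform how the intervention is strengthened and targeted. A need for more toolkit time and a need for more highly trained support call for different actions, and this contrast cannot tell them apart. The grade imbalance is a separate and avoidable source of bias.

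**Working it through.** **1. Provider against group.** As Table 1 describes it, all 21 trial schools were supported by program staff and all 19 later schools by resource persons. Within 1 vs 2.1, a provider indicator would equal the group indicator, so its effect cannot be estimated separately. Stated training is about 100 hours against a minimum of 20, a ratio of at most about 100/20 = 5.

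**2. Expected duration.** The protocol gives no table of years exposed that can be read here (Figure 3 is not shown). I assume on-time progression to the end of Primary 7, attendance at the same school throughout, continued delivery, a trial start between mid-2012 and the start of 2013, and a later start at some point in 2015. Duration = end of Primary 7 minus start of delivery.

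| Grade at Wave 1 (2014) | End of Primary 7 | Trial, years | Later delivery, years |
|---|---|---|---|
| Primary 5 | end 2016 | 4.0–4.5 | 1.1–2.0 |
| Primary 6 | end 2015 | 3.0–3.5 | 0.1–1.0 |
| Primary 7 | end 2014 | 2.0–2.5 | 0 (not in 2.1) |

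The least exposed trial grade (2.0–2.5) only touches the most exposed later grade (up to 2.0). Expected duration is thus itself almost determined by delivery phase, and adjusting for years exposed would do little to isolate provider. Late entry, grade repetition and school moves would create more overlap in practice.

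**3. Grade mix.** An on-time pupil in Primary 7 in 2014 finishes Secondary 1 at the end of 2015; one in Primary 5 finishes it at the end of 2017. The Primary 7 pupil has two more years in hand before the 2018–2019 survey and had already reached Primary 7 at Wave 1. For the example outcomes of completing Primary 7 and Secondary 1, including Primary 7 pupils in group 1 alone would favour group 1 without any toolkit effect. The retention row of Table 2 does say that last grade completed is assessed in relation to age and Wave 1 grade, which covers part of this, but it does not fix how. The other outcomes have no such statement.

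**4. Precision cost of matching on grade.** The protocol states no detectable difference for 1 vs 2.1. Its own figure, for 1 vs 2.2, sets the basis. With 1201 and 456 participants, 50% prevalence, 80% power, two-sided α of .05 (the article prints .5; only .05 reproduces its result) and no clustering:

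d = (1.96 + 0.84) × √[0.25 × (1/456 + 1/1201)] = 7.7 points, OR 0.73, which agrees with the stated 8% and 0.73.

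Group 2.1 is the remainder: 2402 − 1201 − 456 = 745. I assume 50% prevalence there too.

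- All of group 1 (745 vs 1201): d = 6.5 points.
- Primary 5 and 6 only: the size of this part of group 1 is not given. If both arms have the same grade mix, it is at least about 745. If the two non-implementing schools hold 2/21 of the wait-list arm (114 pupils), it is 1201 × 745/(1201 − 114) ≈ 823. Then d = 7.3 to 7.1 points.
- One grade alone, assuming an even split (about 372 vs 372 to 411): d ≈ 10 points.

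Clustering by school would enlarge all of these.

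**The case against.** The best reply is that the protocol is candid and modest. It calls all analysis exploratory and concedes under Limitations that its comparison groups differ on factors other than exposure. It also plans separate measures of years exposed, time since exposure, age at exposure and scored implementation in 39 schools, lists grade as a possible confounder or modifier, and shows duration by grade in Figure 3. That defeats any charge of concealment or confirmatory error. It does not remove the point: the general caveat does not name provider, its remedy (control for observed confounders) cannot work for a factor identical to group, and grade adjustment is left open.

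Several stronger readings are tempting, and the document does not support them:

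- *The intervention section contradicts Table 1.* A reader who stops at "While the intervention remained the same (see Table 1" might infer this, but the same sentence goes on to disclose the change of provider and cites the table.
- *The plan claims a dose-response.* It never says so; it speaks only of levels of exposure.
- *Later schools lacked termly visits and reviews.* Table 1 says "To ensure more uniformity during the trial, Raising Voices staff visited each school at least once per school term", but the same sentence also lists the residential workshop, which the Who provided row describes for protagonists in each school. The How row gives visits and calls by staff or resource persons alike. Being named for the trial does not show absence later.
- *Training was five times lower.* Five is a ceiling, because 20 hours is a minimum and the resource persons were experienced and coached.
- *A pooled high, medium and low exposure scale must be dropped.* It is offered only as an example, with construction to be documented.

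**Conclusion.** The point holds as one of labelling, interpretation and an avoidable imbalance in one exploratory contrast. The contrast of groups 1 and 2.1 cannot by itself show how much exposure is needed, because provider is fully aligned with group, expected duration nearly so, and grade mix differs by design. The provider and grade-mix statements follow directly from the text. The duration table rests on on-time progression, no change of school and the assumed start dates. The direction of the grade bias is clear for the example retention outcomes and not established for the rest. The planned contrasts 1 vs 2 and 1 vs 2.2 are outside this point. Since the article reports that data analysis has not been conducted, the change is worth making.

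**What to change.** For 1 vs 2.1:

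1. Restrict group 1 to trial-school participants who were in Primary 5 or 6 at Wave 1.
2. Report Primary 5 and Primary 6 separately, each against the same grade, and also combined with adjustment for grade.
3. Describe the result as earlier, longer, program-staff delivery against later, shorter, resource-person delivery, and state that it is not used on its own as evidence on how much exposure is needed.
4. Where years exposed or implementation intensity is analysed, also show results within each delivery phase, since only there is provider held constant. A pooled scale can stay alongside.

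The cost is a few sentences and extra output from models already planned, with smaller groups and wider intervals. Before clustering, the detectable difference goes from about 6.5 to about 7.1–7.3 points combined and to about 10 points within a single grade, on the assumptions given in the working. That is acceptable for hypothesis-generating work.

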## Results

Data collection started in 2014 (Wave 1) and data collection was completed in 2019 (Wave 2). Data analysis has not been conducted.

## Discussion

### Principal Findings

This is the first study that evaluates the long-term impacts of an effective primary school violence-prevention intervention in a resource-constrained setting, where the majority of adolescents transition out of school after primary education. Guided by our conceptual framework, we plan to explore how long-term effects on violence and other outcomes may vary across schools and adolescents to build a picture of what works and for whom. This analysis will shed light on the generalizability of effects to inform intervention strengthening, future targeting, and generate hypotheses on potential transferability to other contexts. For instance, if there are no long-term impacts on retention in school, violence outcomes, or factors supportive of resilience, then this will suggest that further efforts are required to reinforce and sustain positive effects. Findings might point toward the need for complementary interventions in secondary schools or targeting family support and the home environment. Little is known about whether capabilities gained in primary school can be maintained through transition into new schools or the workplace, nor whether experiencing improved relationships and school connectedness in a safer primary school environment can positively influence future peer and intimate relationships among older Ugandan adolescents. Our findings will highlight important areas for further qualitative and quantitative inquiry to better understand how school interventions shape violence and other outcomes through adolescent transitions.

### Limitations

This protocol focuses on adolescent long-term outcomes, therefore, whether the intervention is maintained in primary schools and the influence of secondary school environments on outcomes are questions beyond the scope of the analysis. Our quasi-experimental nonrandomized design utilizes the trial delivery and later delivery of the intervention to schools and makes use of an unexposed comparison group that arose from the process and timing of delivery. As in other nonrandomized studies, confounding is of concern, as comparison groups differ regarding factors other than exposure to the intervention. To address this, we have a documented conceptual framework, plan to control for potential observed confounding in our analyses, and will consider the consistency of effects when interpreting results [74]. We expect to gain further insight into the toolkit’s long-term effectiveness by comparing effects across original study arms in addition to across other exposure groupings.

This is an unblinded study, where both participants and researchers—including those leading the analysis—are aware of the intervention delivery. Selection bias may be introduced at Wave 1 as 10% of students in the original trial endline did not agree to follow-up. Differences in retention at Wave 2 could be associated with our outcomes of interest or with toolkit exposure, we will test for differences and, where possible, apply appropriate statistical methods to take account for such differences.

### Conclusion

This analysis will be the first to examine the long-term effects of a whole-school violence-prevention intervention in a resource-constrained setting. If results are positive, this indicates that primary school interventions are promising platforms to institute lasting widespread change. This is especially relevant to alleviate the burden of many adverse outcomes of early exposure to violence in Uganda and other countries.

## Abbreviations

CoVAC: Contexts of Violence in Adolescence Cohort study
OR: odds ratio
WHO: World Health Organization
